### Study outcomes

Table 
1 indicates the **adherence**, **graft**, and **adverse** outcomes being measured in all participants. The planned primary outcome is daily "*taking adherence*", defined as the proportion of daily prescribed doses taken, as measured using electronic monitoring (EM). Because no one method of measuring adherence is considered a gold standard, we will measure adherence in several ways including pharmacy dispensing records, self-report using the MAM-MM, and variability in tacrolimus or sirolimus trough levels
[36-38]. We will also consider a composite of variability in tacrolimus or sirolimus trough levels and self-report such as the ‘system for integrated adherence monitoring’
[39].

**Table 1 T1:** Outcome measures

**Category**	**Measures**	**Frequency**
**Adherence outcomes**	**Electronic monitoring**	Continuously monitored
	● Taking adherence (% prescribed doses taken each day)	
	● Timing adherence (% doses taken within 2 hours of scheduled time each day)	
	● Drug holidays (missing ≥2 consecutive doses)	
	**Pharmacy refills**	All refills during study interval
	● Taking adherence (% prescribed doses taken over entire intervention period)	
	**Variability in tacrolimus or sirolimus trough levels**	Monthly levels as measured for clinical care
	● Standard deviation calculated over 6-month intervals	
	**Self-report** (Medical Adherence Measure- Medication Module)	3-month intervals
	● Taking adherence (% prescribed doses taken, in 3-month intervals)	
	● Timing adherence (% doses taken within 2 hours of scheduled time, in 3-month intervals)	
	● Drug holidays (missing ≥2 consecutive doses)	
**Graft outcomes**	**Graft failures or deaths** (# failures/person-year of follow-up)	All failures during study interval
	● Failure defined as loss of graft function requiring return to dialysis or death from any cause	
	**Acute rejections** (# rejections/person-year of follow-up)	All rejections during study interval
	● Biopsy-proven and presumed rejections, defined as rejections diagnosed by the treating physician based on >20% rise in creatinine	

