### Statistical analysis plan

The primary analysis will use intention-to-treat principles; as-treated secondary analyses will also be done. Daily taking adherence will be determined for each participant for each day of follow-up
[45]; the median daily taking adherence will be determined for participants in each of the intervention and control groups, and plotted against time. This will allow assessment of changes in adherence over the intervention interval for each group. We will calculate the area under the curve (AUC) for the entire intervention interval for each group, and compare AUCs using a two-sided, independent two samples t-test or Wilcoxon test. Greater AUC will reflect greater adherence. To account for possible imbalances between groups, and to test for differences in the patterns of change in taking adherence over time between the intervention and control groups, we will use linear mixed-effects models, adjusting for potential confounders. We will use the same approach to analyze the secondary adherence outcomes.

Percent change in estimated glomerular filration rate (eGFR) over the intervention interval will be compared between groups using a 2-sided, independent two samples t-test or a Wilcoxon rank sum test, as appropriate to the distribution of the data. Acute rejections and graft failures will each be expressed as a rate per person-month of observation, and compared between intervention and control groups using Poisson regression.

The multivariable linear mixed-effects models developed for the primary aim will be extended to include center and system characteristics and accessibility factors that are fixed over time (i.e. Canada vs. US), as well as time-varying center, system, and accessibility variables (i.e. insurance status, perceived accessibility). Similar analyses will be undertaken considering secondary adherence outcomes. We will use these models to identify center, system, and accessibility characteristics that are independently associated with adherence.

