### Power considerations

Our preliminary electronic monitoring studies in adolescent transplant recipients found a mean (±standard deviation (SD)) taking adherence of 79% ± 33 at one site and 78% ± 29 at another site (unpublished). With 75 participants per group, setting alpha at 0.05, we will have 85% power to detect a 20% difference in taking adherence, using a two group t-test, assuming a common SD of 32 (40% of the mean). Preliminary studies suggested substantially lower variability in adherence after intervention compared with before. If the SD is 25% in the intervention group, and 40% in the control group, we will have 95% power to detect a 20% difference in taking adherence, or 80% power to detect a 16% difference. Based on preliminary studies indicating a 26% improvement in adherence after intervention with dose reminders, and on published work
[12], it is reasonable to expect a 20% improvement in adherence when a single level intervention is applied. Effect sizes may be larger with a multi-level intervention.

Due to low event rates and large variability in graft function, statistical power is extremely limited to detect differences between intervention and control groups for graft outcomes; these analyses are considered exploratory.

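### Poisson regression is named for acute rejections, which can recur in one participant, with no stated allowance for overdispersion (minor point)

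*Protocol article*

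**What the plan says.** All places are in the protocol article.

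- **Study outcomes, Table 1, graft outcomes.** Acute rejection is a rate, "rejections/person-year of follow-up", and the frequency column reads "All rejections during study interval". Events are therefore counted, not only first events. The definition is broad: "Biopsy-proven and presumed rejections, defined as rejections diagnosed by the treating physician based on >20% rise in creatinine".
- **Statistical analysis plan.** "Acute rejections and graft failures will each be expressed as a rate per person-month of observation", and the rates are then "compared between intervention and control groups using Poisson regression". One method thus serves both a recurrent count (rejection) and an outcome that in practice occurs once per participant (graft failure or death). No robust variance, dispersion parameter, negative binomial model or participant effect is mentioned.
- **Power considerations.** "Due to low event rates and large variability in graft function, statistical power is extremely limited" for graft outcomes, and "these analyses are considered exploratory". No numerical rejection rate is given.

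Table 1 uses person-years and the analysis section person-months. This is only a change of unit and leaves the rate ratio and its test unchanged.

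**The concern.** Standard Poisson regression takes the variance of each participant's count to equal its mean. That holds if participants in an arm share one underlying rate. If some carry a persistently higher risk, their rejections cluster, the variance exceeds the mean, and the model-based standard error of the log rate ratio is too small.

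The article gives reasons to expect unequal risk. Interquartile ranges for years since transplant are 0.8 to 7.5 and 1.5 to 8.4 in the two arms (Table 2). Preliminary taking adherence was 79% with SD 33 at one site and 78% with SD 29 at another (Power considerations). The Background treats non-adherence as a major contributor to poor graft survival.

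Comparing graft outcomes between arms is a stated secondary aim, so a rejection rate ratio with an interval will probably be published. If that interval is too narrow, a few participants with repeat rejections in one arm could make chance look like an effect. The eGFR comparison described just before allows the test to depend on the distribution of the data. The rejection comparison has no such allowance.

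**Working it through.** **The plan's own figures.** The article states no rate, power or error rate for rejections, so there is nothing to reproduce on this outcome. Its main power statement concerns adherence: "With 75 participants per group, setting alpha at 0.05, we will have 85% power to detect a 20% difference in taking adherence". With SD 32 and the 20% read as relative to a mean of 79 (0.20 x 79 = 15.8 points), power is 85.6% by the normal approximation and 85.2% by the t distribution, so that figure reproduces. Only the 75 per group and the 5% level are carried forward.

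**Inputs.**
- From the article: 75 completers per group, alpha 0.05, a 12-month intervention interval (taken as one person-year each), all rejections counted.
- Assumed, because the article gives neither: mu, rejections per person-year, 0.05 to 0.5; theta, the variance of a gamma-distributed relative risk with mean 1, from 0 (everyone shares one rate) to 4.

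**Formulas.**
- Variance of a participant's count = mu x (1 + mu*theta), so variance/mean = 1 + mu*theta.
- The model-based standard error is too small by sqrt(1 + mu*theta).
- Large-sample type I error at nominal 5% = 2 x (1 - Phi(1.96 / sqrt(1 + mu*theta))).

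Example with mu = 0.3 and theta = 2: 1 + 0.6 = 1.6; sqrt(1.6) = 1.265; 1.96/1.265 = 1.549; type I error = 0.121.

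**Results under no treatment effect.** Simulated columns: 40,000 trials per setting, Wald test of the log rate ratio with either the Poisson variance or a participant-level sandwich variance.

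| mu | theta | SE factor | Large-sample error | Simulated, model-based | Simulated, robust |
|---|---|---|---|---|---|
| 0.05 | 2 | 1.049 | 0.0617 | 0.0129 | 0.0089 |
| 0.1 | 0 | 1.000 | 0.0500 | 0.0353 | 0.0351 |
| 0.1 | 1 | 1.049 | 0.0617 | 0.0424 | 0.0368 |
| 0.1 | 2 | 1.095 | 0.0736 | 0.0508 | 0.0390 |
| 0.1 | 4 | 1.183 | 0.0976 | 0.0694 | 0.0451 |
| 0.2 | 2 | 1.183 | 0.0976 | 0.0906 | 0.0536 |
| 0.3 | 0 | 1.000 | 0.0500 | 0.0447 | 0.0474 |
| 0.3 | 1 | 1.140 | 0.0856 | 0.0766 | 0.0509 |
| 0.3 | 2 | 1.265 | 0.1213 | 0.1172 | 0.0576 |
| 0.3 | 4 | 1.483 | 0.1864 | 0.1765 | 0.0636 |

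What the table shows:

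1. With theta = 0 the error does not exceed 5%, although participants can have several rejections. Repeat events alone do no harm; unequal risk does.
2. At 0.1 per year or below with theta up to 2, the model-based Wald test is at or below about 5%, because sparse events make it conservative.
3. At 0.3 per year the error is about 8%, 12% and 18% for theta 1, 2 and 4. Robust variance brings it to 5.1% to 6.4%.
4. Over mu 0.1 to 0.5 and theta 0 to 4, the robust test stays between 3.5% and 6.4%. At 0.05 per year it is conservative (below 1%).

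A likelihood-ratio test behaves differently at low rates. It gives 7.9% at mu = 0.05 and 6.0% at mu = 0.1 even with theta = 0. That is a sparse-data effect, separate from overdispersion, although the error rises further with theta.

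**How much heterogeneity the article's own gradient implies.** The Background cites an 8% higher graft-failure hazard per 10% decrement in adherence. With SD 32, the log-hazard SD is 3.2 x ln(1.08) = 0.246, so theta is about 0.246 squared = 0.06. At mu = 0.3 the variance ratio is 1 + 0.3 x 0.06 = 1.018 and the error about 5.2%. Adherence by itself, on that gradient, does not create a material problem. Theta of 1 or more needs other sources, such as time since transplant or a tendency of rejection to recur in the same participant.

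**The case against.** The strongest reply is that the article says only Poisson regression. A reader might infer a commitment to model-based standard errors, but the text does not say so. Poisson regression with robust standard errors fits the same sentence, and a condensed article may leave the variance estimator to a fuller plan that is not shown. This stands as a limit: the article is incomplete on the point, and no false statement has been found. What remains is that it names one model for a recurrent and a once-only outcome alike, without distinguishing them.

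A second tempting reading is that counting repeat rejections in itself makes the intervals too narrow and the false-positive rate too high. The theta = 0 rows refute that. The harm is conditional on unequal risk, and at the low event rates the article describes, a Wald test may show no inflation at all.

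A third is that the rejection rate ratio is the trial's main clinical evidence. The article does not support this. The primary outcome is electronically monitored adherence, and the graft analyses are declared exploratory, so no confirmatory conclusion rests on this test. The exploratory label limits what may be concluded; it does not repair the coverage of a reported interval.

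Finally, the adherence gradient cited in the Background gives a theta of only about 0.06. That is fair against large inflation from adherence alone. It concerns graft failure rather than rejection, and it leaves out the other sources of variation.

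**Conclusion.** The point holds in conditional form and is minor. The article names Poisson regression for a count that allows repeat events and does not say how overdispersion is handled. If rejection risk varies between participants, which is likely, model-based standard errors are too small by sqrt(1 + mu*theta).

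The direction is well founded. The size is not fixed by the article: the rates, the gamma form of the heterogeneity and its variance are all assumed, with 75 per arm and one year each. Within those assumptions, type I error of the Wald test runs from about nominal or lower (0.1 per year or below, theta up to 2) to about 8% to 18% (0.3 per year, theta 1 to 4). The concern is limited to acute rejection and does not touch the primary analysis.

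**What to change.** State that acute rejections will be compared by Poisson regression with log follow-up time as offset and participant-level robust (sandwich) standard errors, or by a negative binomial model. Report the number of participants with at least one rejection in each arm, so that a result driven by a few participants is visible. Graft failure or death can keep the Poisson rate. If a fuller analysis plan already specifies this, a cross-reference is enough.

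The cost is one sentence and a somewhat wider interval for the rejection rate ratio where counts are overdispersed. Data collection and sample size do not change. The change does not cure sparse data: with very few events any of these large-sample tests remains approximate, which is a further reason to show the participant counts.

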### Study population

TAKE-IT will enrol 176 kidney transplant recipients between 11 and 24 years old, who are at least 3 mo. post-transplant, and have a functioning graft. Patients with neurocognitive disabilities severe enough to preclude participation in study procedures, those taking immunuosuppressive medications exclusively in liquid formulation, and those unable to communicate comfortably in English (or French – Montreal sites only) will be excluded.

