### Randomization and blinding

Participants are randomized at enrolment in age strata (11–13 y., 14–16 y., 17–19 y., 20–24), by site, in blocks of 4. Allocation to intervention or control group is concealed from participants, clinical care providers, and study personnel at enrolment and during the first two months of the run-in period. Group allocation is revealed to study personnel one month prior to the 3-month visit. Blinding is not feasible to maintain with the proposed multi-component intervention.

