### Progress

Recruitment began in February 2012. Figure 
4 shows the numbers of patients in the eligible age range who were screened, enrolled, and randomized to date. As of March 31, 2014, 130 of the 198 adolescents who were approached had agreed to participate (66%). Table 
2 shows the demographic, medical, and treatment characteristics, by group, of the 125 participants with known randomization allocation to date. Reasons for refusal fall into 3 general categories: 25% refused to meet with study personnel to hear more about the study; 50% felt that they had no problem with adherence and therefore had no reason to participate; 25% felt it would take too much time or would add expense.

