**Figure 4 F4:**
[figure not shown]
**As of March 31, 2014, 268 patients in the eligible age range had been screened for participation.** Of these, 70 met exclusion criteria (including significant neurocognitive disability, inability to communicate in English or French, imminent graft failure, imminent transfer to adult care). Of the 198 who were eligible to participate, 130 agreed (66%) and had completed a baseline visit. Randomization occurs 1 month before the 3-month visit; 125 participants had been randomized as of March 31, 2014.

**Table 2 T2:** Baseline demographic and disease/treatment characteristics of participants randomized to date

	**Control**	**Intervention**
n	64	61
Male (%)	39 (60.9)	34 (55.7)
Median age (IQR)	15.9 (13.6 – 17.5)	16.2 (14.0 – 17.8)
Race (%)		
White	42 (65.6)	43 (70.5)
Black	9 (14.1)	6 (9.8)
Asian	4 (6.3)	3 (4.9)
American Indian/Alaska Native	2 (3.1)	1 (1.7)
Hawaiian/Other Pacific Islander	2 (3.1)	0 (0)
Other	5 (7.8)	8 (13.1)
Hispanic (%)	4 (6.3)	7 (11.5)
Median years since transplant (IQR)	3.7 (0.8-7.5)	4.4 (1.5-8.4)
Primary disease (%)		
CAKUT	30 (46.9)	21 (34.4)
Glomerulonephritis	3 (4.7)	6 (9.8)
FSGS	6 (9.4)	9 (14.8)
Other	23 (35.9)	21 (34.4)
Missing	2 (3.1)	4 (6.6)
Number of immunosuppressive medications (%)		
1	3 (4.7)	4 (6.6)
2	27 (42.2)	21 (34.4)
3	34 (53.1)	35 (57.4)
4	0 (0.0)	1 (1.6)
Median total number of all medications (IQR)	6 (5 - 9)	7 (5 - 9)

*CAKUT* Congenital anomalies of the kidneys and urinary tract, *FSGS* Focal and segmental glomerulosclerosis.

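### The acute-rejection comparison names no covariate; time since transplant, already collected and not a randomisation stratum, should be prespecified in it (minor)

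*Protocol article*

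**What the plan says.** In the protocol article, the Statistical analysis plan section treats the two outcome families differently. For taking adherence, the AUC comparison is followed by a modelling step meant partly to deal with chance differences between the arms: "we will use linear mixed-effects models, adjusting for potential confounders". The scope is then widened, but only within adherence: "We will use the same approach to analyze the secondary adherence outcomes".

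The next paragraph covers graft outcomes. Percent change in eGFR gets a t-test or a rank-sum test. Acute rejections and graft failures are turned into rates per person-month and "compared between intervention and control groups using Poisson regression". No covariate is named.

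The Randomization and blinding section gives the strata: "Participants are randomized at enrolment in age strata (11–13 y., 14–16 y., 17–19 y., 20–24), by site, in blocks of 4". Time since transplant is not among them. The Study population section admits patients "who are at least 3 mo. post-transplant, and have a functioning graft", so recent and long-standing recipients enter together. Table 2, in the Progress section, describes the "125 participants with known randomization allocation to date". Its row beginning "Median years since transplant (IQR" shows 3.7 (0.8-7.5) for 64 controls and 4.4 (1.5-8.4) for 61 intervention participants.

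The Power considerations section describes the graft-outcome analyses as exploratory, with very little power.

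**The concern.** Time since transplant is plausibly prognostic for acute rejection. It varies widely here, is recorded for the participants in Table 2, and is left to simple chance by the stratification. All three reported quartiles are lower in controls, and the lower quartile is about half that of the intervention arm. If rejection is more frequent soon after transplant, a two-group rate comparison of these arms would lean towards the intervention even with no effect. The plan recognises the general problem and states a remedy for adherence, but not for rejection, although comparing graft outcomes is a stated secondary aim.

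What is at stake is the point estimate of an exploratory outcome. With few events, that estimate is what readers are likely to carry away.

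**Working it through.** The article gives no rejection rate, no early-versus-late rate ratio and no power figure for rejection, so there is no stated figure to reproduce. What follows is a range under stated assumptions.

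**1. Is the Table 2 gap more than chance?** Taking SD as IQR width / 1.349: control (7.5 - 0.8)/1.349 = 4.97; intervention (8.4 - 1.5)/1.349 = 5.11. The standard error of a difference in means is sqrt(4.97²/64 + 5.11²/61) = 0.90, so a gap of 0.7 years has z = 0.7/0.90 = 0.78. On the median scale the standard error is 1.253 × 0.90 = 1.13 and z = 0.62. Resampling 64 and 61 participants from the pooled, interpolated distribution gives a median gap of at least 0.7 years about 56% of the time, and a lower-quartile gap of that size about 27% of the time. The gap is compatible with chance.

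**2. How much intervention-period follow-up is early?** Assume baseline time since transplant x is piecewise linear through the Table 2 quartiles, with a minimum of 0.25 years (the entry criterion). The intervention year runs from month 3 to month 15, so a participant is followed from x + 0.25 to x + 1.25 years.

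- One-year boundary: the early time contributed is max(0, 0.75 - x), which integrates over x from 0.25 to 0.75 to 0.125. Control: density 0.25/0.55 = 0.4545, giving 0.4545 × 0.125 = 5.7% of follow-up. Intervention: density 0.25/1.25 = 0.20, giving 0.20 × 0.125 = 2.5%.
- Two-year boundary: the early time contributed is min(1, max(0, 1.75 - x)). Control: 0.2273 + 0.0222 + 0.0389 = 28.8%. Intervention: 0.1000 + 0.0938 + 0.0027 = 19.6%.

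**3. Expected rate ratio with no intervention effect.** With k the early/late rate ratio and p the early share of follow-up in each arm, RR = (1 + (k - 1)p_I) / (1 + (k - 1)p_C).

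| Boundary | k = 2 | k = 3 | k = 5 |
|---|---|---|---|
| 1 year | 1.025/1.057 = 0.97 | 1.050/1.114 = 0.94 | 1.100/1.227 = 0.90 |
| 2 years | 1.196/1.288 = 0.93 | 1.393/1.577 = 0.88 | 1.786/2.153 = 0.83 |

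A smoothly falling hazard, t^-0.25, t^-0.5 or t^-0.75, integrated over the same months gives 0.96, 0.91 and 0.86, and barely changes with an assumed maximum of 12 to 18 years. Table 1 counts all rejections in the study interval. If the run-in were counted too (months 0-15), the one-year ratios would be 0.95, 0.91 and 0.85 and the two-year ratios 0.93, 0.89 and 0.84, still within 0.97-0.83.

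**4. Size against precision.** Assume 150 person-years and 0.05, 0.10 or 0.20 rejections per person-year, so 7.5, 15 or 30 events split evenly. The 95% interval multiplies or divides the rate ratio by exp(1.96 × 2/sqrt(events)) = 4.2, 2.8 or 2.0. On the log scale, the largest shift (0.83) is 0.19/0.72 = 26% of the interval's half-width at 30 events and 0.19/1.43 = 13% at 7.5 events.

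**The case against.** The strongest objection is that the article does not say the model is unadjusted. Poisson regression carries covariates readily, and a condensed article may leave the covariate list for an exploratory outcome to a full protocol or SAP that is not shown. This stands to the extent that a reader should not infer that the plan rules out adjustment. What remains is that the article states adjustment for one outcome family and a bare between-group comparison for the other.

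A reader might also infer from Table 2 a bias built into the design in favour of the intervention. The documents do not support that. The table is interim, the gap is compatible with chance, the final imbalance is unknown, and randomisation favours neither arm in expectation.

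Nor is the largest tempting figure right. By the same interpolation, about 27% of controls and 15% of intervention participants are under one year post-transplant at baseline. Putting those shares into the formula gives ratios of 0.91, 0.85 and 0.77 for k = 2, 3 and 5. That treats each such person as early for the whole intervention year. With entry at 3 months or later and a 3-month run-in, intervention time starts at least 6 months after transplant, and anyone beyond 0.75 years at baseline contributes no first-year time. On the same one-year boundary the ratios are 0.97, 0.94 and 0.90.

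Finally, choosing a covariate because it looks unbalanced is poor practice. That is correct, and the case for this one should rest on its expected prognostic value.

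**Conclusion.** The point holds as a minor improvement. As stated, the rejection comparison leaves out a collected, plausibly prognostic covariate that randomisation does not balance by design, while the same section adjusts the adherence models. Given the interim allocation, the null rate ratio would sit at about 0.97-0.83, a spurious reduction of 3-17%.

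That range rests on three assumptions: rejection is two to five times as frequent in the first one or two years (or falls as the power laws above), the Table 2 quartiles can be interpolated linearly, and the final allocation resembles that of the first 125 participants. The first has no support either way in the article. The shift is small against an interval that spans at least a factor of two each way at the assumed event rates. The plan already labels the outcome exploratory, and the primary outcome is not touched.

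**What to change.** In the acute-rejection Poisson model, prespecify log time since transplant at the start of the intervention (the 3-month visit) as a covariate. Give expected prognostic value as the reason, not the Table 2 difference, and fix the choice before rejection is compared by arm. Report the adjusted rate ratio with the unadjusted one beside it. If a full protocol or SAP already contains this, no change is needed there beyond confirming it.

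The cost is a sentence of analysis-plan wording and one degree of freedom. Time since transplant is already collected. With perhaps 8 to 30 events under the assumed rates, one continuous term is affordable, but the gain in precision will be limited and a longer covariate list would not be sensible.

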**Figure 1 F1:**
[figure not shown]
Common barriers to medication adherence are indicated, along with the components of the TAKE-IT intervention that address each.

A secondary aim of TAKE-IT is to compare the intervention and control groups with respect to graft outcomes. Another secondary aim is to identify independent associations between adherence and healthcare system factors, including characteristics of the treating team, insurance status, Canadian vs. American system, and accessibility to care.

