## Methods/Design

### Study organization

Figure 
2 shows the organizational structure of the 8 kidney transplant centers across Canada and the United States participating in TAKE-IT. TAKE-IT adheres to the Declaration of Helsinki, and was approved by the Research Ethics Boards of all sites (McGill University Health Centre Research Ethics Board, The Hospital for Sick Children Research Ethics Board, University of British Columbia Children’s and Women’s Health Centre Research Ethics Board, The Children’s Hospital of Philadelphia Institutional Review Board, The Washington University in St. Louis Human Research Protection Office, The Seattle Children’s Hospital Institutional Review Board, The Cincinnati Children’s Hospital Medical Center Institutional Review Board, and the Centre Hospitalier Universitaire Ste-Justine Research Ethics Board). Informed consent is obtained from all participants and/or parents.

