### Additional data

#### Treating center and healthcare system characteristics

Information
[42] regarding practice patterns and characteristics of the healthcare organization will be collected from each of the sites. Examples include number of kidney transplant patients followed at the center, whether a dedicated pharmacist or psychologist regularly interacts with patients as a part of the transplant team, the patient: full-time transplant nurse ratio, methods that patients may use to communicate with the treating team (phone/email/text message), and the frequency of clinic visits and blood monitoring for stable patients. Additional factors
[42], indicating characteristics of the healthcare system within which the patient is cared for (adult vs. pediatric, Canadian vs. U.S.), healthcare insurer, medication insurer, and average monthly out-of-pocket expenses will also be recorded.

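### Eight centres cannot support independent attribution of adherence to several centre-constant factors, and the plan does not label that analysis exploratory

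*Protocol article*

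**What the plan says.** Under Study aims, the protocol article states this secondary aim: "identify independent associations between adherence and healthcare system factors, including characteristics of the treating team, insurance status, Canadian vs. American system, and accessibility to care". Study organization refers to "the 8 kidney transplant centers across Canada and the United States participating in TAKE-IT".

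The section on treating center and healthcare system characteristics describes what will be collected from each site, by way of examples: "number of kidney transplant patients followed at the center, whether a dedicated pharmacist or psychologist regularly interacts with patients", then the ratio of patients to transplant nurses, the available means of communication, and "the frequency of clinic visits and blood monitoring for stable patients". It also records adult or pediatric care, country, insurers and out-of-pocket cost.

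The Statistical analysis plan section adds fixed and time-varying centre, system and accessibility variables to the mixed models built for the primary aim, plans similar analyses for the secondary adherence outcomes, and concludes: "We will use these models to identify center, system, and accessibility characteristics that are independently associated with adherence".

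Power considerations describes only the graft-outcome analyses as exploratory. It gives no power or precision figure for the centre and system aim.

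**The concern.** A factor that takes one value per centre is informed by differences between centres, however many participants each centre contributes. With 8 centres, a handful of such factors uses up nearly all of that information. The plan nevertheless promises to name which characteristics are associated with adherence after allowance for the others.

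If the aim is carried out as worded, a chance difference among a few centres could be published as the effect of a health system or a staffing pattern. Readers would have no signal that this part of the paper is weaker than the rest.

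**Working it through.** **Inputs from the protocol article**
- Centres: 8 (Study organization). The ethics boards listed there appear to be four Canadian and four US; this split is inferred from institution names.
- Planned completers: 150 (Recruitment), so 150 / 8 = 18.75 per centre on average.
- SD of taking adherence: 32 points (Power considerations).
- Centre-level examples: patients followed, pharmacist, psychologist, nurse ratio, communication methods, visit frequency, blood-monitoring frequency. That is seven; country makes eight.

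**Assumed:** the intraclass correlation between centres (ICC), which the article does not give. A range is shown.

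The plan states no figure for this aim, so there is none to reproduce.

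**Step 1: separability (needs no ICC).** Eight centres give 8 distinct rows for centre-constant factors. With *k* such factors and an intercept, residual centre df = 8 − 1 − *k*, as long as the columns are not aliased.

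| Centre-constant factors | Parameters | Residual centre df | Two-sided 5% critical t |
|---|---|---|---|
| 1 | 2 | 6 | 2.45 |
| 3 | 4 | 4 | 2.78 |
| 5 | 6 | 2 | 4.30 |
| 6 | 7 | 1 | 12.71 |
| 7 | 8 | 0 | none |
| 8 | 9 (rank 8) | 0 | not identifiable |

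More participants per centre change nothing here. A centre random effect corrects the standard errors but does not separate the factors.

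**Step 2: what one factor could show.** For a balanced 4 versus 4 contrast, SE = √[32² × (ICC + (1 − ICC)/18.75) × (1/4 + 1/4)].
- ICC 0.01: √(1024 × 0.0628 × 0.5) = 5.67
- ICC 0.05: √(1024 × 0.1007 × 0.5) = 7.18
- ICC 0.10: √(1024 × 0.148 × 0.5) = 8.70

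With 6 df, the noncentral t gives 80% power at about 3.37 × SE: differences of 19, 24 and 29 points. With five mutually orthogonal factors (2 df) the figures are 32, 41 and 49 points. Treating 150 participants as independent would suggest 2.802 × 32 × √(2/75) = 14.6 points.

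**Step 3: only if the model has no centre term.** Design effect = 1 + (18.75 − 1) × ICC. The approximate true size of a nominal 5% test is 2 × Φ(−1.96/√design effect).

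| ICC (assumed) | Design effect | Approximate type I error | Simulated, 4 vs 4 centres of 19 |
|---|---|---|---|
| 0.02 | 1.355 | 9.2% | 9.4% |
| 0.05 | 1.89 | 15.4% | 15.7% |
| 0.10 | 2.78 | 23.9% | 24.6% |

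The simulation used 5,000 null data sets per setting. Tests on centre means kept their size (4.9% to 5.3%).

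**The case against.** The case on the other side has four parts.

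- **The list is not a model.** The practice characteristics are examples of data to be collected, and the article does not say that all enter one model together. This stands: a reader might infer that the planned model is certain to be unidentifiable, and the text does not support that. The point does not depend on it, because three to five terms already leave only 4 to 2 df.
- **Some factors may vary within a centre.** Participants may come from affiliated adult clinics, the plan mentions time-varying centre variables, and access to phone, email or text support is also recorded at enrolment under Accessibility to care. These could add some information. They cannot help a factor such as country, which is fixed in each centre. If communication access is moved to the participant level, seven factors remain, and seven leave no residual df.
- **The random-effect structure is not given.** A reader might infer that participants will be analysed as independent across centres. The article does not say so; it names linear mixed-effects models and leaves the levels open, as a condensed article reasonably may. The type I error figures are therefore conditional, and the silence is not itself a fault.
- **The quoted sentence covers more than centre factors.** Insurance, out-of-pocket cost, distance and perceived access vary between participants, and multivariable adjustment is legitimate for them. This stands and limits the scope of the point.

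**Conclusion.** The point holds for centre-constant factors. The article states an inferential aim, independent association, that 8 centres cannot deliver for several such factors at once. That conclusion rests on the count of centres and on the practice factors being essentially constant within a centre. It does not rest on any assumed ICC or on the choice of random effects.

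The size is 7 between-centre degrees of freedom in all, 4 to 2 left after three to five factors, and none after seven. Even a single balanced factor could be detected with 80% power only at differences of about 19 to 29 points, under an assumed ICC of 0.01 to 0.10, equal centre sizes and an SD of 32.

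Inflated type I error of about 9%, 16% and 25% is a further risk only if the model omits a centre term. It depends on the assumed ICC (0.02, 0.05, 0.10), about 19 participants per centre and the inferred 4 versus 4 country split.

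It would be wrong to infer that the trial's main result is at risk: randomization is stratified by site, so the intervention comparison is not affected.

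**What to change.** Under Study aims and in the Statistical analysis plan:

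1. Label the analysis of centre-constant factors (practice characteristics and country) exploratory, and drop the word *independently* for them.
2. Enter these factors one, or very few, at a time, in a model with a centre random intercept and centre-level small-sample degrees of freedom (for example Kenward-Roger or between-within).
3. Keep multivariable adjustment, and the language of independent association, for factors that vary between participants: insurance, out-of-pocket cost, distance and perceived access.

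If the full analysis plan already has a centre random effect, only the degrees of freedom, the limit on terms and the wording remain to be settled. No data collection changes. The cost is a more modest secondary claim and wider intervals for centre-level factors.
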